## Abstract

**Background:**

Much implementation research is focused on full-scale trials with little evidence of preceding modelling work. The Medical Research Council Framework for developing and evaluating complex interventions has argued for more and better theoretical and exploratory work prior to a trial as a means of improving intervention development. Intervention modelling experiments (IMEs) are a way of exploring and refining an intervention before moving to a full-scale trial. They do this by delivering key elements of the intervention in a simulation that approximates clinical practice by, for example, presenting general practitioners (GPs) with a clinical scenario about making a treatment decision.

**Methods:**

The current proposal will run a full, web-based IME involving 250 GPs that will advance the methodology of IMEs by directly comparing results with an earlier paper-based IME. Moreover, the web-based IME will evaluate an intervention that can be put into a full-scale trial that aims to reduce antibiotic prescribing for upper respiratory tract infections in primary care. The study will also include a trial of email versus postal invitations to participate.

**Discussion:**

More effective behaviour change interventions are needed and this study will develop one such intervention and a system to model and test future interventions. This system will be applicable to any situation in the National Health Service where behaviour needs to be modified, including interventions aimed directly at the public.

**Trial registration:**

ClinicalTrials (NCT): NCT01206738

## Background

Although much is known about interventions that can be effective in changing the behaviour of health professionals [1], the literature provides little information to guide the choice, or to optimise the components, of these interventions [2,3]. Implementation research is the scientific study of methods to promote the uptake of research findings to improve the quality of care. However, much implementation research is focused on full-scale trials with little evidence of preceding modelling work. The Medical Research Council (MRC) framework for developing and evaluating complex interventions has argued for more and better theoretical and exploratory work prior to a trial as a means of improving intervention development [4].

The use of intervention modelling experiments (IMEs) for interventions that aim to change behaviour is one approach to doing exploratory work [5]. In an IME key elements of the intervention are delivered (generally in a randomised controlled trial, hence use of the word 'experiment') in a manner that approximates the real world but the measured outcome is generally an interim outcome, a proxy for the clinical behaviour of interest (clinical decision in response to a simulated clinical encounter) prior to entering the intervention into a full-scale trial. To date IMEs have been paper-based [5,6] but this may limit their efficiency, acceptability and ecological validity. Web-based IMEs have the potential to provide much richer simulations of clinical encounters and allow measurement of key process variables such as time to make a decision. The current study will develop a web-based IME system based around an existing web-based intervention delivery system called Lifeguide http://www.lifeguideonline.org/[7]. We will then use the new system to run a web-based IME on antibiotic prescribing for upper respiratory tract infections (URTIs) in general practice.

Cochrane reviews of the effectiveness of antibiotics in treating URTIs suggest no benefit in colds [8] and only marginal benefit for uncomplicated sore throat [9]. A large cohort study of the use of antibiotics for respiratory tract infection in UK primary care concluded that antibiotics are not justified to reduce the risk of serious complications in URTIs [10]. Primary care accounts for 80% of total antimicrobial use and 60% of that is for respiratory infections, which are on the whole self-limiting [11]. The web-based IME will systematically develop and evaluate theory-based interventions for reducing unnecessary prescribing of antibiotics that correspond to the theoretical, modelling and experimental phases of the MRC framework. We will directly compare this work with a previously published paper-based IME on the same topic [6], allowing us to evaluate the two methods of developing and simulating interventions prior to a full-scale trial. We propose that the most effective intervention will go on to be evaluated in a separately funded full-scale trial.

### Trial objectives

1. To run a web-based IME to develop and evaluate theory-based interventions to reduce antibiotic prescribing for URTIs in primary care.

2. To compare the effectiveness of email and postal invitations to general practitioners (GPs) to take part in the web-based IME in a randomised controlled trial.

3. To compare the web-based and paper-based methods of running IMEs in terms of identification of predictors, the type of intervention that can be simulated, and the effect on intended prescribing behaviour on trial conduct of an IME.

## Methods

### Trial design

#### General

The study will include two trials, one a web-based IME, the other an evaluation of the method used to invite GPs to take part in the web-based IME. The basic design of these two trials will be:

1. Web-based IME: a three-arm, double-blind, randomised controlled trial of two behaviour change interventions compared to generic information.

2. Invitation: a two-arm, randomised controlled trial of an email invitation to GPs compared to a postal invitation.

The web-based IME will be based on a previous paper-based IME [6]. This earlier work provided qualitative data about the kind of attitudes and beliefs among GPs about the use of antibiotics in the treatment of URTIs (cough/cold, sore throat/tonsillitis in patients of any age). This was used to develop questionnaire items relevant to the clinical context of treating URTIs in primary care and which operationalised the constructs of our chosen theories (*e.g*., theory of planned behaviour: questionnaire has an item asking GPs whether they thought patients expected them to prescribe an antibiotic, which is linked to the theory's subjective norms construct). The earlier work also developed clinical scenarios describing patients presenting in primary care with symptoms of URTI. GPs were asked to report their clinical decisions in response to the scenarios and these were used to generate scores for 'simulated behaviour.' We will use a web-based IME to deliver the questionnaire and scenarios to GPs in order to identify predictors of prescribing behaviour and compare these with those identified in the paper-based IME.

The research study is based in the Division for Clinical and Population Sciences and Education at the University of Dundee at Ninewells Hospital, with support from the Universities of Aberdeen, Newcastle and Southampton and the Scottish School of Primary Care. It is funded by the Chief Scientist Office, grant number CZH/4/610 and approved by the Tayside Committee on Medical Research Ethics A, REC reference 10/S1401/54. A flow diagram of the study is shown in Figure 1.

**Figure 1 F1:**
[figure not shown]
**Flow diagram - Randomised controlled web-based IME with an embedded trial of email versus postal invitation to participate**.

#### Participants

Inclusion criterion is GPs in Scotland. Exclusion criterion is the inability to obtain both an email address and a postal address for the GP.

#### Identifying participants

GPs will be identified by the Scottish Primary Care Research Network (SPCRN; http://www.sspc.ac.uk/spcrn/) [12] using a combination of publicly available information provided by ISD Scotland http://www.isdscotland.org/isd/3793.html[13] and restricted information held on the NHS.net database. A preliminary test of our recruitment method has identified over 3,000 GPs for whom we can obtain both email and postal addresses.

GPs receiving a postal invitation will receive a one-page letter and a two-page information sheet. Together with general information, the letter will contain a URL to the web-based IME system and a unique identifier for the GP. The identifier will be used to identify non-responders and for payment (see below). GPs receiving an email invitation will receive an email containing the same text as on the paper letter and the two-page information sheet as a pdf attachment. We will send two reminders to non-responders, the first at two weeks, the second at four weeks, using the same method as used for the initial invitation. We expect response rates of 30% to 40% based on the earlier paper-based IME [6].

Participants will be asked to complete up to two online questionnaires, which together will form a web-based IME. GPs will be paid £20 in advance in the form of a voucher for the first part of the web-based IME and £30 in advance as a voucher for the second part. A recent Cochrane review of strategies to increase response rates to postal and electronic questionnaires found that advanced payment led to a higher response rate (odds ratio = 2.00; 95% confidence interval = 1.54 to 2.60) [14]. GPs will be able to select from a list of seven types of voucher: Amazon, Argos, Boots, iTunes, Love2Shop, Marks & Spencer, or Starbucks. GPs will also be free to do the study without receiving a voucher if they so wish.

GPs will be able to decline to take part in the study by clicking a button on the second page of the web-based IME system, by emailing their ID number to a study email address, or by telephoning or sending a text message to the study mobile number. A flow diagram of the study is shown in Figure 1.

#### Informed consent

GPs will not be expected to provide explicit consent; a completed questionnaire will be taken as implied consent.

#### Randomisation

The study statistician will generate a list of random numbers to be used by SPCRN to randomly allocate GPs to receive either an email or postal invitation on a 1:1 basis. There will be no stratification. The list will be generated using Stata 11.0 statistical software (StataCorp, College Station TX). To ensure we do not approach too many GPs to participate in the main study we will randomise two initial blocks of 250 GPs (see Sample size) then subsequent blocks of 50 GPs will be contacted until the required sample size for the web-based IME is met.

All GPs will complete the same, initial web-based questionnaire to identify predictors of behavioural intention and simulated behaviour. GPs will receive one of two interventions (one of which will be a persuasive communication) or a comparator with the second web-based questionnaire. The study statistician will generate a list of random numbers for allocation to intervention or comparator on a 1:1:1 basis, which will be loaded into the web-based IME system. Allocation will, therefore, be done by the system when the GP logs onto the web-based IME system to complete the second questionnaire. There will be no stratification.

#### Blinding

Study participants, the trialists, and the trial statistician will be blind to allocation. Staff at the SPCRN will know the allocation for the email versus postal invitation study but not the web-based IME intervention study.

#### Trial procedures

Participants will be asked to complete up to two online questionnaires, which together will form a web-based IME. GPs who are already likely to be following best evidence with regard to prescribing antibiotics will be excluded from the second questionnaire, which we will do by excluding those in the first quartile of 'intention to prescribe' responses to the first questionnaire. These 25% of GPs will be thanked but will not continue in the study. Thus 75% of GPs completing the first questionnaire will be asked to complete the second. The intervention will be delivered together with the second questionnaire.

#### Duration

Participants will remain in the study until they complete the second questionnaire, which we expect to be between four and five months after they receive the invitation to take part.

### Interventions and comparator

#### Interventions

The web-based IME will deliver one of the interventions used in the paper-based IME [6] -- a persuasive communication -- and a second, new intervention developed for the web-based IME. The persuasive intervention aimed to reinforce the GP's beliefs about the positive consequences of managing sore throat without prescribing antibiotics. The materials for the persuasive communication can be downloaded at http://www.biomedcentral.com/content/supplementary/1472-6963-8-11-s2.doc[15]. This intervention did change GPs' beliefs in the paper-based IME, and we aim to see if this is replicated in the web-based IME.

However, we will also deliver a new intervention that takes advantage of the possibilities of web delivery. This will allow a comparison between an intervention simulated using web and paper-based methods and, additionally, provide a head-to-head comparison between that intervention and an intervention developed without the constraints of paper delivery.

The new intervention, designed to take advantage of the possibilities offered by web-based delivery, will be designed using predictors identified from the first questionnaire and by using appropriate behaviour change techniques [16,17]. There is no widely agreed taxonomy by which to specify methods of delivery of behaviour change techniques; we will use as a starting point the suggestions of the Evidence-based Behavioural Medicine Committee (EBMC) [18]. Suggested dimensions are: provider, format, setting, recipient, duration, and frequency. We will use the EBMC suggestions to map the effectiveness of the interventions in the primary studies included in the systematic reviews populating it with the delivery methods used in the studies in the systematic reviews of strategies to decrease antibiotic prescribing [19,20] and the results from the first questionnaire. We will send the results of the mapping exercise to a small number of experts for external validation.

We will use 'intervention mapping' [21] to systematically consider combinations of content and methods of delivery; there are likely to be logical combinations. By considering such combinations we will produce a range of potential new interventions.

We will pilot each of the potential new interventions (up to three) with groups of three to six GPs. Whilst delivering the intervention we will ask them to 'think aloud' about their reactions to the intervention, which allows us to identify problems and fine-tune content and delivery. We will select the most promising intervention for evaluation in the web-based IME. GPs involved in developing the intervention will not be included in the web-based IME.

#### Comparator

The comparator will be provision of general information about prescribing of antibiotics taken from recent reviews on antibiotic prescribing [8,9].

#### Outcome measures

For the web-based IME, the primary outcomes will be behavioural intention and behavioural simulation, which have been shown to be reliably related to behaviour [16,22]. Three questions will assess GPs' strength of intention to manage URTIs without antibiotics (*e.g*., over the next 12 weeks, when a patient presents with a URTI, I have in mind to manage them without prescribing an antibiotic (rated on 7-point Likert scales 'Strongly Disagree' - 'Strongly Agree'). Responses will be summed with a low score corresponding to a low intention to prescribe antibiotics. Sixteen clinical scenarios from the paper-based IME work will provide the materials to measure simulated behaviour (eight in the first questionnaire, eight more in the second). Respondents will be asked how they will manage the patients in the scenarios and asked to rate, on a score out of 10, the difficulty of making their clinical decision.

Secondary outcomes are concerned with evaluating the relative utility of web-based and paper-based IMEs. For this, we will compare the following outcomes for each method.

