##### 6. Effect size for persuasive communication intervention compared to control

The persuasive communication intervention and control were delivered in an earlier paper-based IME. By delivering the same intervention in a web-based IME we can compare the effect on the primary outcome (intention to prescribe an antibiotic) of the two delivery methods. Here, we are looking for the greatest effect size.

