### Statistics

#### Sample size

Our sample size will be 250 GPs completing the first questionnaire, 75% of whom will be invited to complete the second questionnaire. GPs who are already likely to be following best evidence with regard to prescribing antibiotics will be excluded from the second questionnaire, which we will do by excluding those in the first quartile of 'intention to prescribe' responses to the first questionnaire. These 25% of GPs will be thanked but will not continue in the study. For the first questionnaire analysis, our required sample size will be 162 based on a recommendation by Green [23] for multiple regression analysis with 14 predictor variables. The analysis of the questionnaire data will check the internal consistency of the measures and use multiple regression analysis to examine the relationships between predictor and outcome variables.

Using the dependent variable of behavioural intention, we will seek to detect an effect size of 0.66. This was the mean effect size for change in intention in a meta-analysis of trials that measured change in intention and behaviour [24]. This 'medium to large' change in intention led to a 'small to medium' change in behaviour. We will require 50 participants per group to have 90% power of detecting this effect size at a significance level of 5% to 150 participants in total. We anticipate having 187 GPs in our 75% sample from the first questionnaire study, which will allow for some dropout.

The effect of each intervention will be estimated by comparing the change in intention in each of the active intervention groups with that in the control group. This procedure will be repeated with behavioural simulation as the dependent variable. We propose to take the intervention with the largest effect size forward into a definitive trial; there is a risk of wrongly choosing this as the most effective (a type 3 error). With 50 practitioners per group if treatment B is actually superior to treatment A, such that the standardised difference in mean scores is 0.38, the probability of incorrectly choosing treatment A is 5%.

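### The go-forward rule names no deciding outcome: the plan has two primary outcomes, powers only intention, and gives no answer if the two rank the interventions differently

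*Protocol article*

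**What the plan says.** The web-based experiment is "a three-arm, double-blind, randomised controlled trial of two behaviour change interventions compared to generic information", with "allocation to intervention or comparator on a 1:1:1 basis" (Protocol article, General and Randomisation).

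The section Outcome measures says that "the primary outcomes will be behavioural intention and behavioural simulation". Item 6 of the secondary outcomes, on the persuasive communication, speaks in the singular of "the primary outcome (intention to prescribe an antibiotic".

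The section Sample size works from one outcome: "Using the dependent variable of behavioural intention, we will seek to detect an effect size of 0.66". It arrives at 50 per group for 90% power at the 5% level. Each active group is to be compared with control on change in intention, and then "This procedure will be repeated with behavioural simulation as the dependent variable". The next sentence gives the decision rule: "We propose to take the intervention with the largest effect size forward into a definitive trial". The section recognises that this choice may be wrong, calls that a type 3 error, and puts it at 5% for a true standardised difference of 0.38 in unspecified scores.

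The section Statistical analysis plans ANCOVA on both primary outcomes with 95% intervals for each active arm against control. The article states no hierarchy between the outcomes, no rule for conflicting rankings and no multiplicity adjustment.

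**The concern.** The trial exists to choose one intervention for a separately funded full-scale trial. The sentence that makes the choice follows directly on the analyses of both outcomes and names neither. If intention favours one intervention and simulation the other, the written rule cannot be applied, and someone who has seen both results must decide which outcome counts. The type 3 figure has the same gap, since it is not attached to an outcome.

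Two lesser points follow from the same ambiguity. The 90% power is supported for intention only, although simulation is also called primary. And if significance is claimed for either active arm on either outcome, there are four chances to do so, while the 5% level was worked for one.

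**Working it through.** **Inputs from the article:** three arms, 1:1:1; n = 50 per group; effect size 0.66 (SD 1); 90% power; 5% level; selection difference 0.38; 187 GPs expected for the second questionnaire. **Assumed:** two-sided tests, and a correlation ρ between the two outcomes, which the article does not give (range shown).

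**1. Sample size.** n = 2(1.960 + 1.282)² / 0.66² = 48.2, so 49 per group; 49.2, so 50, with the t distribution. Power at 50 per group is 90.4% (t). The stated 50 reproduces.

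**2. Type 3 figure.** On one outcome with a common SD, the control mean cancels when two effects against control are ranked. The difference between the active arms has standard error √(2/50) = 0.20. The chance of a wrong choice at 0.38 is Φ(−0.38/0.20) = Φ(−1.90) = 2.9%, not 5%. A 5% risk matches a difference of 1.645 × 0.20 = 0.33, or about 37.5 per group at 0.38. The printed figure errs on the cautious side.

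**3. How often the outcomes disagree.** Let δ₁ and δ₂ be the true gaps on intention and simulation. Then

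P(disagree) = Φ(−δ₁/0.20) + Φ(−δ₂/0.20) − 2Φ₂(−δ₁/0.20, −δ₂/0.20; ρ).

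| True gaps (intention, simulation) | ρ = 0 | ρ = 0.3 | ρ = 0.5 | ρ = 0.9 |
|---|---|---|---|---|
| 0.38, 0.38 | 5.6% | 5.2% | 4.6% | 2.3% |
| 0.38, 0.19 | 19.0% | 17.7% | 16.6% | 14.3% |
| 0, 0 | 50% | 40% | 33% | 14% |

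By hand at ρ = 0, first row: 2 × 0.0287 × 0.9713 = 5.6%. For equal interventions the formula reduces to ½ − arcsin(ρ)/π, which is 1/3 at ρ = 0.5.

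**4. Family-wise error** (each test two-sided 5%, no true effects, shared control, simulation of 1,000,000 draws). Two contrasts on intention alone: 9.1%. All four tests: 17.3%, 16.9%, 16.1%, 14.9% and 12.6% at ρ = 0, 0.3, 0.5, 0.7 and 0.9.

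**5. Power after adjusting two intention contrasts.** At 50 per group and 0.66, Bonferroni (2.5% each) gives 84.5% (t) or 85.5% (normal). Dunnett, with a critical value of about 2.23, gives 85.6%. Keeping 90% under Bonferroni needs 57 (normal) to 59 (t) per group, that is 3 × 57 = 171 to 3 × 59 = 177 in total.

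**6. Simulation.** The article gives no expected effect on this outcome, so its power cannot be computed. As a purely assumed range, unadjusted power at 50 per group is 17% at 0.2, 41% at 0.35 and 70% at 0.5.

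**The case against.** The strongest reply is that the plan does not leave the choice unexamined. It names the risk of picking the wrong intervention and quantifies it. The rule ranks effect sizes and uses no significance test, so family-wise error does not drive it. The article defines no success criterion based on a p-value, this is a modelling study ahead of a full trial, and a multiplicity method may sit in an analysis plan that is not shown. All of that stands. A reader might infer that the choice has no error control; the documents do not support this. If one intervention is better by 0.38 on both outcomes, the chance of a wrong choice is 2.9% on either outcome alone and lower still if the largest effect over both decides.

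Item 6 may also simply identify which primary outcome is used in the comparison with the paper-based study. That is a fair reading, so the singular wording is supporting evidence and not a contradiction on its own.

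A reader might further infer, from the remark that a sizeable change in intention led to a smaller change in behaviour, that simulation is underpowered by a known amount. The remark concerns behaviour in a meta-analysis, not scenario scores. Moreover, the planned baseline adjustment would raise power above the unadjusted figures.

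None of this supplies the missing element: which outcome decides, and what happens when the two conflict.

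**Conclusion.** The point holds as a gap in the decision rule. Two outcomes are primary, one has a sample-size basis, and the choice of intervention is attached to neither. The chance that this matters is about 5% if one intervention is better by 0.38 on both outcomes, 17–18% if the gap on simulation is half that (ρ 0.3–0.5; 19% at ρ = 0), and 33–50% if the interventions are equal (ρ 0–0.5). The true gaps and ρ are assumptions.

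A reader might construct a much worse case. If the interventions differ by 0.33 on intention and not at all on simulation, the outcomes disagree in 46–48% of trials, and taking the largest effect over both errs about 12% of the time (ρ 0.3–0.5). But simulation is then a coin toss by construction, and nothing in the article supports that scenario over the others.

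The family-wise error of about 13–17% for four tests, against about 9% for two, applies only if significance is claimed against control. The 90% power applies to intention only.

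**What to change.** Before any second-questionnaire data are seen, state that:

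- the intervention taken forward is the one with the larger ANCOVA-adjusted standardised difference from control on behavioural intention, in the direction of less prescribing, with the same SD used for both arms;
- simulation is reported as supportive and does not decide the choice;
- the type 3 error figure refers to intention, with its inputs rechecked (0.38 and 50 per group give 2.9%);
- the 90% power applies to intention only.

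Align Outcome measures and item 6 with this. Making simulation a formally gated secondary outcome is a design preference and is not needed to close the gap.

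If significance is to be claimed for either active arm, test the two intention contrasts with Holm or Dunnett at an overall 5%.

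The cost is wording. With adjustment, unadjusted-for-baseline power per contrast at 50 per group falls from 90% to about 85–86%. Keeping 90% takes 57–59 per group. The 171–177 needed lie within the expected 187, but leave room for only 10 to 16 losses (about 5–9%), against 37 (about 20%) under the present target of 150. Baseline adjustment would ease this by an amount that the article does not allow one to compute.
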